**Discussion:**

In this trial, we target the thromboinflammatory response at multiple levels. We intensify the dose of low molecular weight heparins to reduce thrombotic complications. Aprotinin is a potent kallikrein pathway inhibitor that reduces fibrinolysis, activation of the contact pathway of coagulation, and local inflammatory response. Additionally, aprotinin has shown in vitro inhibitory effects on SARS-CoV-2 cellular entry. Because the excessive thromboinflammatory response is one of the most adverse prognostic factors in COVID-19, we will add anakinra, a recombinant interleukin-1 receptor antagonist, to the regimen in case of severely increased inflammatory parameters. This way, we hope to modulate the systemic response to SARS-CoV-2 and avoid disease progressions with a potentially fatal outcome.

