### Trial design {8}

This study is part of the larger DAWn consortium. The DAWn-Antico study is an adaptive, randomized, parallel-group open-label multicenter clinical trial to evaluate the safety and efficacy of promising agents in hospitalized adult patients diagnosed with COVID-19. The study is a phase 2 proof-of-concept multicenter trial program in patients with COVID-19. The adaptive study design of DAWn allows for the addition of new treatment and strata during the study based on the most updated information.

With a 2:1 randomization, the DAWn-Antico study evaluates standard thromboprophylaxis (low molecular weight heparin (LMWH) at 50 IU/kg once daily in hospitalized patients and twice daily in patients on intensive care units) with a multi-step antithrombotic and anti-inflammatory strategy (Fig. 2). This strategy consists of the following:
A.A higher prophylactic dose of subcutaneous LMWH: 50 IU/kg twice daily in hospitalized patients and 75 IU/kg twice daily in patients on intensive care units from day 0 to 15, ANDB.Aprotinin 2 × 10^6^ KIE 4 times per day as intravenous (IV) infusion from day 0 to 3 for a total of 72 h (3 × 4 doses)C.Additionally, patients with biochemical signs of hyperinflammation at baseline or during follow-up will receive add-on interleukin-1 receptor blockage by anakinra 100 mg 4× daily. Hyperinflammation is defined as an absolute lymphocyte count < 1000 cells/mL and two of the following: (1) ferritin > 800 ng/mL, (2) LDH > 400 U/L, or (3) D-dimers > 1000 ng/mL.

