#### Inclusion criteria

Male or non-pregnant female adult ≥ 18 years of age at the time of enrolmentConfirmed diagnosis of SARS-CoV-2 infection, defined as *either*:
SARS-CoV-2 PCR positive within 72 h before randomization*or*Respiratory infection symptoms (fever, cough, dyspnea, desaturation) and typical findings on chest CT scan and absence of other plausible diagnoses.In patients without PCR-confirmed diagnosis at inclusion, all efforts will be made to confirm definite SARS-CoV-2 infection (e.g., PCR on bronchial aspirate, PCR on BAL fluid or serologic testing). Participants who—despite all efforts—do not have a confirmed diagnosis of COVID-19 will be excluded from the analysis.Illness of any duration and at least one of the following:
Radiographic infiltrates by imaging (chest x-ray, CT scan, etc.) *or*b.Clinical assessment (evidence of rales/crackles on lung auscultation) ANDSpO2 ≤ 94% on room air *or*c.Requiring mechanical ventilation and/or supplemental oxygen.

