### Who will take informed consent? {26a}

Potential participants are screened on the emergency ward or upon arrival at the COVID-ward. Accordingly, an emergency physician or a supervising physician at the COVID-ward who is trained in the protocol will first assess the patient’s interest in the study, if necessary through the legal representative. If there is an interest in participating, the investigators of the DAWn-study team again check the eligibility criteria and contact the patient or legal representative to provide more information and obtain informed consent. When signed informed consent is not permitted because of safety regulations related to the prevention of the transmission of SARS-CoV-2, the ethical committee approved the use of verbal informed consent. The consent form is read and illustrated by the investigator on the phone, and the patient or legal representative gives verbal consent which will be documented in the medical records, all in the presence of a witness. Signed informed consent shall then be obtained as soon as permitted based on safety regulations to prevent the transmission of SARS-CoV-2. The process for obtaining and documenting initial and continued informed consent from potential trial participants will be conducted following the International Conference on Harmonization of Technical Requirements for Registration of Pharmaceuticals for Human Use–Good Clinical Practice or ICH-GCP E6(R2), applicable regulatory requirements, and internal standard operating procedures (SOPs).

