#### Secondary outcomes

Secondary outcomes include clinical outcomes and markers of thromboinflammation at predefined time points. A summary is listed below; the detailed list is provided in the full protocol attached.
Clinical status and time to clinical improvementMortality (day 15, day 28, time to death)Duration of supplemental oxygen, mechanical ventilation, hospitalization, ICU stay, time to live weaning, and time to live dischargeUsages and doses of rescue anti-inflammatory therapy (such as corticosteroids, IL-1 or IL-6 blockers—non-limitative)Adverse eventsStandard laboratory valuesMarkers of hyperinflammation (CRP, ferritin, LDH, interleukin profile)Markers of thrombotic activation and kallikrein-bradykinin activation (D-dimers, fibrinogen, PT, aPTT, C1-inhibitor, factor XII)Markers of adrenal function (cortisol, ACTH, albumin/transcortin)Combined cardiac endpoint during hospitalizationIncidence of thrombotic events and major bleeding complications during hospitalization as per ISTH criteria

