### Sample size {14}

Sample size estimates provided serve as a reference, but not as an indication of the final number of patients to be randomized.

In the pilot phase of DAWn-AntiCo, we will evaluate the effect of modulation of the thromboinflammatory response on biochemical parameters. To evaluate the effect of this strategy, we will evaluate the difference in mean D-dimers on day 6. Published data show highly variable D-dimer values in patients with COVID [2, 3]. For an estimated mean D-dimer of 1000 with a standard deviation of 600, a sample size of 51 patients (17:34 with 1:2 randomization) has a power of 0.8 and an alpha of 0.05 to detect a difference of 500. We will therefore evaluate the effect of the intervention after a pilot phase of 60 (20:40) patients. Based on the information from other DAWn studies, the final sample size for effect on clinical outcomes will be evaluated following this pilot phase.

In their study comparing clinical improvement rates for lopinavir-ritonavir in hospitalized patients with severe COVID-19, Cao et al. reported a clinical improvement rate in the control group of 37.7% on day 14 [25].

Therefore, for our sample size calculations, we assume that a 40% improvement rate will be observed on day 15 in the control group, which yielded an expected hazard ratio of 1.5632. Since all missing clinical status data up to day 15 will be imputed, we assumed no censoring of the data prior to day 15. Based on the log-rank test, with a 2-sided significance level of 5% and 80% statistical power and using a (2:1) randomization ratio in favor of the intervention, we estimate that a total sample size of 354 patients will suffice to detect an absolute improvement of 15% (i.e., 55% in the intervention group). To detect an absolute improvement of 20% (60% in the intervention group), a total sample of 196 patients will suffice. We propose a pragmatic sample size of 210 patients taking into account early dropouts.

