#### Analysis of the secondary endpoint(s)

Cumulative clinical status up to day 15 will be analyzed using a general linear model adjusted for clinical status on day 0. The treatment effect will be estimated by the difference of mean values between the groups.Cumulative clinical status recorded daily during the hospital stay and on days 15 and 19 will be analyzed using a proportional odds logistic regression model, adjusted for clinical status on day 0. The common odds ratio will estimate the treatment effect.All-cause mortality rates will be estimated by the treatment group using the Kaplan-Meier method. The resulting Kaplan-Meier curves will be compared using a log-rank test. The treatment effect will be estimated by the hazard ratio using a Cox regression.Time-to-event parameters with competing risk (time to clinical improvement, composite cardiac endpoint): event rates will be estimated using cumulative incidence functions (CIF), and the resulting CIF curves will be compared using Gray’s test. The subdistribution hazard ratio will estimate the treatment effect.Duration of hospital and ICU stay: both parameters will be analyzed as time-to-event parameters with competing risk, whereby the event of interest is discharged from hospital/ICU, and the competing risk is hospital/ICU death.Continuous normally distributed variables (e.g., QTc) will be analyzed using a 2-sample *t* test. Treatment effects will be estimated by the difference in mean values between the groups. If applicable, changes from baseline will be calculated. Comparisons between treatment groups will be made by performing an analysis of covariance (ANCOVA) on the post-baseline value, using the baseline value as a covariate.Continuous non-normally distributed variables (clinical status, NEWS score, duration of supplemental oxygen, duration of mechanical ventilation) will be analyzed using a Wilcoxon rank-sum test. Change in ordinal scale at specific time points will be compared using Wilcoxon rank-sum tests.The proportion of patients with D-dimer < 1000, ferritin < 1000, and LDH < 600 on day 6 and day 15 will be compared.The proportion of patients who develop hyperinflammation at days 3, 6, and 15; time to hyperinflammation.

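### The ICU-stay analysis uses events that a patient who never enters the ICU cannot have, so it gives no sound randomized comparison of ICU use; the bias can go either way

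*Protocol article*

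**What the plan says.** Under Analysis of the secondary endpoint(s), one sentence covers both durations: "both parameters will be analyzed as time-to-event parameters with competing risk, whereby the event of interest is discharged from hospital/ICU". The same sentence then names what competes with that event: "and the competing risk is hospital/ICU death". Read in pairs, ICU stay is time to ICU discharge with ICU death as the competing event. The article does not give the time origin, the analysis set, or the handling of a patient who is never admitted to the ICU.

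The population includes patients outside the ICU:

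- Recruitment (Who will take informed consent? {26a}): "Potential participants are screened on the emergency ward or upon arrival at the COVID-ward". Recruitment {15} says the same.
- Entry (Inclusion criteria): one qualifying route is "Requiring mechanical ventilation and/or supplemental oxygen", so oxygen alone is enough.
- Dosing in the intervention arm (Trial design {8}) distinguishes the two settings: "50 IU/kg twice daily in hospitalized patients and 75 IU/kg twice daily in patients on intensive care units".

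The abstract's Discussion gives the aim as to "avoid disease progressions with a potentially fatal outcome".

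Objectives {7} lists incidence and ventilator-free days for mechanical ventilation. Neither that list nor Secondary outcomes has an ICU counterpart, although the latter is a summary and "the detailed list is provided in the full protocol attached".

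**The concern.** A time-to-discharge analysis needs every patient to start in the state that is to be left. That is true of the hospital but not of the ICU. For a patient randomized on the ward, ICU admission comes after randomization, and it is something the strategy is meant to influence. An analysis that depends on admission no longer compares the groups as randomized, and fewer admissions earn no credit.

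Two further gaps follow from the wording. A ward patient who dies without reaching the ICU has neither event. A patient who leaves the ICU and then dies on the ward has already had the favourable event.

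The stake is a secondary result on ICU use that could mislead. Trial design {8} tests secondary hypotheses without a hierarchy, so such a result could be reported on its own.

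**Working it through.** The plan states no figure on this point, so there is none to reproduce. The check has two parts: which event each type of patient can have, and an illustration on assumed inputs.

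**Events under the stated rule (paired reading)**

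| Patient | ICU discharge | ICU death |
|---|---|---|
| In ICU at day 0 | possible | possible |
| Ward at day 0, admitted to ICU later | possible | possible |
| Never in ICU, survives | impossible | impossible |
| Never in ICU, dies on ward | impossible | impossible |
| Leaves ICU, dies on ward | occurs, counted as discharge | no |

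If the slash is read more broadly, so that any hospital death competes with ICU discharge, the fourth row gains a competing event. The third and fifth rows do not change.

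**If never-admitted patients are left out**

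Assumptions, none from the documents: 1,000,000 simulated patients; 30% enter the ICU; severity s is standard normal; stay = exp(ln 8 + 0.6s + 0.5e) days with e standard normal; probability of ICU death = 1/(1 + exp(1.1 − s)), about 29% overall. The treatment prevents one third of admissions and has no other effect. Deaths are treated as never discharged, as in a cumulative incidence function.

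| Admissions prevented | Median time to live ICU discharge, admitted patients | Discharged alive by day 14 | ICU days per randomized patient |
|---|---|---|---|
| None (control) | 10.3 d | 59% | 3.27 |
| Mildest third | 16.7 d | 45% | 2.77 |
| Random third | 10.3 d | 59% | 2.18 |
| Most severe third | 6.8 d | 76% | 1.41 |

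The measured stay gets longer, stays the same or gets shorter, while ICU use falls each time. If the mildest third is prevented and the remaining stays are also cut by 40%, the median is 10.0 days, so the two effects nearly cancel.

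**If never-admitted patients stay at risk without an event**

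Assume 30% against 20% admitted, 29% ICU mortality in both arms, and prevention unrelated to severity.

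- Final cumulative incidence of ICU discharge, control: 0.30 × 0.71 = 0.213.
- Intervention: 0.20 × 0.71 = 0.142.
- Approximate subdistribution hazard ratio: ln(1 − 0.142)/ln(1 − 0.213) = ln 0.858/ln 0.787 = 0.64.

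A treatment that only prevents admissions appears to delay discharge.

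**One scenario under three handling rules**

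Take the mildest-third scenario, with cumulative incidence of ICU discharge by day 7:

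- left out: 36% control, 18% intervention;
- kept at risk: 0.30 × 0.359 = 10.8% and 0.20 × 0.176 = 3.5%;
- scored as discharged at day 0: 81% and 84%.

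The third rule points the opposite way from the other two. The answer depends on a rule that the article does not give.

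**The case against.** The strongest reply is that the article does not say never-admitted patients are dropped. Scoring them as zero days is not ruled out, and a journal article may leave the analysis set and time origin to the full protocol or the analysis plan. This stands in part: silence on handling is not itself a fault. But the article does fix the event and the competing event, and these do not fit a patient who never enters the ICU. Scoring at day 0 would be an added rule. It would record a discharge that never happened, and it would do so even for a ward patient who later dies.

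A reader might infer that preventing ICU admissions must lengthen the measured stay, and might put a percentage on that. The documents do not support this. It requires the prevented admissions to be the shorter stays, and nothing in the article says which admissions the strategy would prevent. The illustration gives all three directions.

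Three other points stand. The share of patients in the ICU at day 0 is not given; for them admission happened before randomization and cannot be affected by treatment. Averted deterioration also shows in ventilation incidence, ventilator-free days, clinical status and mortality, so ICU stay would not be read alone. Hospital stay is sound in this respect.

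**Conclusion.** The point holds in limited form. As stated, the ICU-stay analysis does not give a valid comparison of ICU use between the randomized groups. It either depends on admission after randomization or counts avoided admissions as failures to be discharged. Under the first reading the sign of the bias is unknown: longer apparent stay if milder admissions are prevented, shorter if severe ones are, none if prevention is unrelated to severity. Under the second, avoided admissions read as harm.

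No size can be given for this trial, because the documents report no ICU admission rate, length of stay or ICU mortality. The figures above show direction only and rest on the stated assumptions. The conclusion needs only that some patients are randomized outside the ICU, which the recruitment and entry rules imply, and that treatment may affect admission, which is part of its aim.

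This is one part of one secondary outcome. It should be corrected, but it does not touch the primary endpoint.

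**What to change.** - Keep the competing-risk analysis for hospital stay.
- For the ICU, compare days alive and out of the ICU to day 28 in all randomized patients: 28 for a survivor never in the ICU, 0 for death by day 28. Adjust for day 0 clinical status and show the result next to mortality. This parallels the ventilator-free days already listed, and it also accounts for deaths on the ward by day 28, before or after an ICU stay.
- Report length of stay among admitted patients descriptively only, or restrict the time-to-ICU-discharge model to patients in the ICU at day 0. In that model, state how a death on the ward after ICU discharge is counted.

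The cost is wording in the statistical analysis plan, which the article says is finalized before database lock. Day 28 mortality is already an outcome, and the ICU-stay endpoint already implies that ICU dates are recorded. The downside is that ICU-free days mixes mortality with ICU use, hence the need to show mortality beside it.

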## Statistical methods

### Statistical methods for primary and secondary outcomes {20a}

#### Analysis of the primary efficacy endpoint

The primary endpoint will be analyzed using competing risk analyses whereby death without any improvement will be considered as a competing risk. Event rates will be estimated using cumulative incidence functions (CIF). Median times to improvement will be calculated by the treatment group.

The effect of treatment will be assessed by performing a Fine and Gray competing risk regression model that includes the baseline clinical status value on day 0 as a covariate and randomized treatment as a factor. From the Fine and Gray model, the treatment effect and associated 95% confidence interval will be estimated.

In the pilot phase of DAWn-Antico, the effect of modulation of thromboinflammation will be evaluated on a laboratory primary efficacy endpoint, mean D-dimer level at day 6. The null hypothesis being tested is that the mean D-dimer level on day 6 is the same for the standard of care and intervention arm. Means will be compared with appropriate statistical testing after checking for normality. The full statistical analysis plan will be finalized before the database lock.

To evaluate the effect of aprotinin and high-dose enoxaparin vs. anakinra, analyses will be performed separately in patients with or without signs of hyperinflammation (i.e., with or without an indication for anakinra in the intervention group).

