### Methods in analysis to handle protocol non-adherence and any statistical methods to handle missing data {20c}

Patients who do not have complete clinical status data up to day 15 will be accounted for as follows:
Single-day missing, with preceding and following day known: in these cases, the missing value will be imputed by the maximum of the two surrounding values.Otherwise: missing data will be imputed using multiple imputation methodology whereby a total of 100 imputations will be done. Clinical status on each day will be imputed consecutively based on the clinical status of the previous days and meaningful clinical variables. When all data have been imputed, the cumulative score up to day 15 will be calculated using the imputed scores. Age, gender, baseline disease severity, and randomized treatment group will be included in the imputation model.

Up to the time of death, missing D-dimers will be imputed using a methodology similar to the one described for the imputation of clinical status. If necessary, a log-transformation will be applied to the D-dimer data to attain a normal distribution for D-dimer. After imputation, to account for deaths before day 6, D-dimer data will be analyzed using a GEE model that evaluates the data over time with an appropriate model.

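### Oxygen and ventilation durations are compared by Wilcoxon test with no rule for death, so the comparison is confounded with mortality whenever mortality differs between arms

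*Protocol article*

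**What the plan says.** In the Protocol article, under Analysis of the secondary endpoint(s), the two support durations are grouped with continuous non-normal variables: "duration of supplemental oxygen, duration of mechanical ventilation) will be analyzed using a Wilcoxon rank-sum test". That item does not say how a patient who dies on support is ranked, or whether patients who never needed the support are included.

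Death is addressed elsewhere in the article:

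- Hospital and ICU stay, same list: "both parameters will be analyzed as time-to-event parameters with competing risk, whereby the event of interest is discharged from hospital/ICU". Dying in hospital or on the ICU is named there as the competing event.
- Other time-to-event secondary endpoints, same list: "Time-to-event parameters with competing risk (time to clinical improvement, composite cardiac endpoint" get cumulative incidence functions, Gray's test and a subdistribution hazard ratio. The oxygen and ventilation durations are not named there.
- Primary endpoint, Analysis of the primary efficacy endpoint: "death without any improvement will be considered as a competing risk".
- D-dimer, section {20c}: "to account for deaths before day 6, D-dimer data will be analyzed using a GEE model".

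The imputation rule in {20c} ("Patients who do not have complete clinical status data up to day 15 will be accounted for as follows") concerns clinical status. The other rule there concerns D-dimer. Neither reaches the durations.

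Objectives {7} also lists oxygenation-free and ventilator-free days, and Secondary outcomes lists time to live weaning. The article does not say how deaths count in them and does not put them in place of the Wilcoxon comparison.

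**The concern.** A duration of support can end in two opposite ways: the patient recovers and is weaned, or the patient dies. A rank test on the raw number of days treats both endings alike. Followed as written, a patient who dies on day 4 of ventilation ranks ahead of a survivor weaned on day 12.

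If mortality is equal in the two arms this adds noise but no bias. If it differs, the test responds to the mortality difference even when recovery is identical in both arms. The article describes severe COVID-19 as having high mortality, makes mortality an outcome, and tests secondary hypotheses without a hierarchy (Trial design {8}). A nominally significant shorter or longer duration could therefore be reported when it reflects only who died and when.

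**Working it through.** **Plan's own figure.** The article gives none for these durations. Its proposed total of 210 at 2:1 gives 70 control and 140 intervention patients, and its alpha is two-sided 0.05.

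**Assumed inputs (not in the documents).** Every patient is on the support. Weaning time is exponential with mean 14 days in both arms. Time of death is exponential with mean 6 days. A decedent stays on support until death. The cap is 28 days. Only mortality differs between arms.

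**Step 1: direction.** Let q be the probability that a decedent's duration is shorter than a survivor's. Ignoring the cap, whose effect is negligible,

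q = 14 / (14 + 6) = 0.70.

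Let m_H and m_L be mortality in the higher- and lower-mortality arms. Pairs of the same type (two survivors or two decedents) contribute 0.5, so the probability that a patient from the higher-mortality arm has the shorter duration is

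θ = 0.5 + (q − 0.5)(m_H − m_L).

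The bias is zero if m_H = m_L, or if q = 0.5 (here, deaths at mean 14 days). It reverses if q is below 0.5.

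**Step 2: size.** The null standard error of θ is √[(70 + 140 + 1) / (12 × 70 × 140)] = √(211 / 117,600) = 0.0424. The chance that the higher-mortality arm is declared shorter is about 1 − Φ(1.96 − (θ − 0.5)/0.0424).

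| Mortality | Mean time of death | θ − 0.5 | Formula | Simulation |
|---|---|---|---|---|
| 20% vs 20% | 6 days | 0 | 2.5% | 2.6% |
| 20% vs 30% | 6 days | 0.20 × 0.10 = 0.020 | 1 − Φ(1.49) = 6.8% | about 7% |
| 20% vs 40% | 6 days | 0.20 × 0.20 = 0.040 | 1 − Φ(1.02) = 15% | 14% to 16% |
| 20% vs 50% | 6 days | 0.20 × 0.30 = 0.060 | 1 − Φ(0.54) = 29% | 28% to 31% |
| 20% vs 30% | 12 days | (14/26 − 0.5) × 0.10 = 0.004 | 1 − Φ(1.87) = 3.1% | about 3% |

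**Step 3: other timing assumptions.** With lognormal time on support (median 12 days, log-SD 0.7) and mortality of 20% vs 30%, the higher-mortality arm is declared shorter in 18.4% of simulated trials if deaths fall on days 1–7 and in 4.0% if they fall on days 7–14. For deaths on days 14–28 the direction reverses: 0.75% shorter, 9.65% longer.

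**Step 4: never-ventilated patients scored 0.** Assume that 15% of survivors and 70% of decedents are ventilated, with mortality of 20% vs 30%. The ventilated share is then 0.8 × 0.15 + 0.2 × 0.70 = 26% in the lower-mortality arm and 0.7 × 0.15 + 0.3 × 0.70 = 31.5% in the higher. The higher-mortality arm now has fewer zeros. In simulation it is declared shorter in under 1% of trials and longer in about 10%.

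**Step 5: death ranked worst.** With the Step 1 inputs and 20% vs 30% mortality, q = 0 and θ − 0.5 = −0.05. The higher-mortality arm is declared worse in 1 − Φ(1.96 − 1.18) = 22% of trials (simulation also 22%) and better in about 0.1%.

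**The case against.** The strongest objection concerns direction. A reader might infer that the arm with more deaths will look better, so that a harmful regimen would appear to shorten support. The documents do not support that as a general statement. Eligibility does not require ventilation or oxygen: radiographic infiltrates alone meet that criterion, and ward patients are enrolled. If all randomised patients enter the ventilation comparison, many may score 0 and the bias can run the other way (Step 4). For oxygen it depends on when deaths occur (Steps 1 to 3). This objection stands, and it limits the point to confounding with mortality, not a sign error in a known direction.

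Second, the larger rates in the table need mortality differences of 20 to 30 percentage points. Mortality has its own Kaplan-Meier, log-rank and Cox analysis, and a data monitoring committee watches safety, so such a difference would be seen beside any result on duration. This also stands and lowers the practical risk.

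Third, a reader might infer that the plan ignores death in respiratory outcomes altogether. That goes too far: time to live weaning and support-free days are listed, and the full protocol and analysis plan, which are not shown, may define a rule for death.

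The third objection does not remove the point. The article does not merely leave the durations open. It fixes a test for them that ignores death, beside a competing-risk analysis for hospital and ICU stay, which are the same kind of variable.

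**Conclusion.** The point holds as a flawed stated method for two secondary endpoints. The Wilcoxon comparison of raw durations is not interpretable as an effect on recovery if mortality differs between arms, and the article's own treatment of hospital and ICU stay is inconsistent with it.

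The direction and size of the bias cannot be fixed from the documents. With everyone on support, survivors' mean 14 days and mortality of 20% vs 30%, the wrong-direction rate is about 7% for deaths at mean 6 days and about 3% for deaths at mean 12 days, against 2.5% nominal. Other plausible assumptions take it to 18.4% or reverse it. With equal mortality there is no bias. The primary endpoint is unaffected, because it already treats death as a competing risk.

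**What to change.** In Analysis of the secondary endpoint(s), remove the two support durations from the Wilcoxon item and adopt one of the following:

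1. Time to live weaning from oxygen and from ventilation, among patients on that support, with cumulative incidence functions, Gray's test and the subdistribution hazard ratio, and death as the competing risk, as for hospital and ICU stay.
2. Oxygenation-free and ventilator-free days, already listed in Objectives {7}, compared in all randomised patients with death scored as the worst value. The time horizon should be stated.

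Report raw durations descriptively only, separately for survivors and decedents, and state which patients are included.

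The cost is a wording change and a little extra programming. The outcomes are already listed, the competing-risk method is already specified, and the analysis plan is still to be finalised before database lock. The price in interpretation is that the estimand is no longer pure duration: option 2 is a composite with death, and option 1 describes weaning in the presence of death. Option 1 also conditions on having received the support, which for support started after randomisation is not a randomised comparison.

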**Fig. 2 Fig2:**
[figure not shown]
Trial design

DAWN-AntiCo will start with a pilot phase powered to detect the biochemical response and will continue to detect the effect on clinical outcomes. In this trial, a superiority hypothesis will be tested with a two-sided type I error rate of 0.05. Secondary hypotheses will be tested in a non-hierarchical way. The statistical analysis plan will be finalized before the database lock.

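### Clinical status, NEWS and change in the ordinal scale get Wilcoxon tests with no baseline covariate, a less efficient choice than the day 0-adjusted models the plan uses elsewhere (secondary endpoints only)

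*Protocol article*

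**What the plan says.** All references are to the protocol article. Under Analysis of the secondary endpoint(s), one bullet states: "Continuous non-normally distributed variables (clinical status, NEWS score, duration of supplemental oxygen, duration of mechanical ventilation) will be analyzed using a Wilcoxon rank-sum test". The next sentence adds: "Change in ordinal scale at specific time points will be compared using Wilcoxon rank-sum tests". Neither mentions a covariate.

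The same section adjusts for baseline in three other places:

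- **Cumulative status:** "Cumulative clinical status up to day 15 will be analyzed using a general linear model adjusted for clinical status on day 0".
- **Status recorded daily in hospital and later:** these records and those "on days 15 and 19 will be analyzed using a proportional odds logistic regression model, adjusted for clinical status on day 0", with a common odds ratio as the effect measure.
- **Normally distributed variables:** treatment groups are compared by "performing an analysis of covariance (ANCOVA) on the post-baseline value, using the baseline value as a covariate".

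Under Analysis of the primary efficacy endpoint, the Fine and Gray model "includes the baseline clinical status value on day 0 as a covariate and randomized treatment as a factor". Day 0 clinical status is therefore on record and treated as prognostic.

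**The concern.** Variables treated as normal are adjusted for baseline. The non-normal ones, which here include a 7-category ordinal scale listed among continuous variables, are not. If day 0 status predicts later status, an unadjusted comparison of the later value discards information that has already been collected.

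The change score does use day 0, by subtraction, but has a different weakness. On the scale under Primary outcome, 7 is death. A death then scores +1 from category 6, +2 from 5, +3 from 4 and +4 from 3. A ventilated patient who dies (+1) ties with a patient who moves from supplemental oxygen to high-flow or non-invasive support (4 to 5, also +1). That patient also ranks better than a survivor who goes from 3 to 5 (+2). Modelling the later category with day 0 as a covariate avoids this.

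At stake are the precision and interpretability of secondary comparisons. No effect measure is named for the Wilcoxon bullet.

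**Working it through.** **1. The plan's own figures.** No power is stated for the Wilcoxon tests. Sample size {14} sizes the clinical phase "with a 2-sided significance level of 5% and 80% statistical power and using a (2:1) randomization ratio in favor of the intervention". With HR = ln(1 − pT)/ln(1 − pC) and events = (1.960 + 0.842)² / [(2/3)(1/3)(ln HR)²]:

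- 40% v 55%: HR = ln 0.45 / ln 0.60 = 1.5632; 177 events; mean event rate (0.40 + 2 × 0.55)/3 = 0.50; N = 354 (stated 354).
- 40% v 60%: HR = 1.794; 104 events; mean rate (0.40 + 2 × 0.60)/3 = 0.533; N = 195 (stated 196).

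These agree to within one patient. The proposed 210 patients at 2:1 are 70:140. The level is two-sided 0.05, as Trial design {8} also states ("a superiority hypothesis will be tested with a two-sided type I error rate of 0.05").

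**2. Normal approximation.** Let ρ be the correlation between baseline and outcome. It is an assumption, shown as a range. With equal spread at both times, the relative variance is 1 for the later value, 2(1 − ρ) for change and 1 − ρ² for the adjusted analysis. Power = Φ(2.802/√v − 1.960), set so that the unadjusted later value has 80%. For example, at ρ = 0.5 the adjusted analysis gives Φ(2.802/√0.75 − 1.960) = 89.9%.

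| ρ | Later value | Change | Adjusted | 210 on later value equal, adjusted: 210(1 − ρ²) | 210 on change equal, adjusted: 210(1 + ρ)/2 |
|---|---|---|---|---|---|
| 0.3 | 80% | 65.8% | 83.6% | 191.1 | 136.5 |
| 0.5 | 80% | 80.0% | 89.9% | 157.5 | 157.5 |
| 0.7 | 80% | 95.1% | 97.5% | 107.1 | 178.5 |

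**3. Simulation on the 7-category scale.** The setting is 70:140, two-sided 0.05, 400 runs. Patients are hospitalised, so day 0 categories are 3 to 6, with assumed probabilities 0.15, 0.50, 0.20 and 0.15. The assumed control distribution over categories 1 to 7 at average baseline is 0.15, 0.25, 0.10, 0.20, 0.08, 0.10 and 0.12. Proportional odds hold, with an assumed treatment odds ratio of 2.2 given day 0 status. The baseline slope is 0, 0.5, 1.0 or 1.5 log odds per category. All three tests use the same simulated trials.

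| Spearman ρ | Wilcoxon, value | Wilcoxon, change | Adjusted proportional odds | Loss, value | Loss, change |
|---|---|---|---|---|---|
| 0 | 85.25% | 75.75% | 85.75% | 0.5 | 10.0 |
| 0.24 | 81.0% | 82.5% | 85.0% | 4.0 | 2.5 |
| 0.43 | 72.25% | 81.5% | 83.5% | 11.25 | 2.0 |
| 0.58 | 60.0% | 76.0% | 80.5% | 20.5 | 4.5 |

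The Monte Carlo standard error near 80% is √(0.8 × 0.2/400) = 2 points. Differences of 2 to 5 points are therefore small and imprecise, while those of 11 and 20 are not. Under no effect, rejection rates were 3.5% to 6.25% across the three methods, against a standard error of √(0.05 × 0.95/400) = 1.1 points.

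**4. Why steps 2 and 3 differ for change.** Step 2 assumes equal spread at both times. In step 3 the day 0 variance is 19.75 − 4.35² = 0.83, while the control outcome variance at slope 0 is 16.73 − 3.59² = 3.84. At ρ = 0 the relative variance of change is (3.84 + 0.83)/3.84 = 1.22, not 2. Entry restricted to hospitalised categories makes step 3 the closer model for the change score.

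**The case against.** The strongest reply is that clinical status is already analysed with day 0 adjustment, by a linear model and by proportional odds with a common odds ratio. This stands. A reader might infer from the Wilcoxon bullet that status is tested only without adjustment, and the article does not support that. For status, the point is duplication by a weaker test.

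A reader might also infer that the change score ignores baseline. It does not, and its power loss is modest at moderate correlations. The case against it there rests on how it scores deaths. It can be said that the primary endpoint also counts points gained on this scale. That is fair for improvement, but the primary analysis treats death without improvement as a competing risk and does not score it as a difference from baseline.

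For NEWS, the article's text states no day 0 value, its summary of secondary outcomes does not list NEWS, and the contents of Table 1 were not available to me. That a baseline NEWS exists cannot be assumed.

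Finally, a Wilcoxon test is valid and does not need proportional odds, so it is a reasonable companion analysis. This stands, and is why the test on status can be kept as supportive. Choosing a lead analysis may fairly be left to the statistical analysis plan, so its absence from the article is not counted here.

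**Conclusion.** The point holds as a minor matter of efficiency and interpretation in secondary endpoints. For the later value of clinical status, the unadjusted Wilcoxon loses essentially nothing at correlation 0, about 4 points at 0.24, about 11 at 0.43 and about 20 at 0.58. For the change score, the loss is about 2 to 5 points at correlations 0.24 to 0.58 and about 10 at 0. These figures rest on the assumed odds ratio, category distributions and correlations. None of these is in the article, so the range matters more than any single value. The NEWS part is conditional on a baseline NEWS being collected.

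A reader might go further and infer an invalid test or an underpowered trial. Neither follows: simulated type I error was close to nominal, and neither the primary model nor the sample size depends on these tests.

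**What to change.** In the secondary analysis section, and in the statistical analysis plan before database lock:

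- Name the proportional odds model adjusted for day 0 status as the analysis of clinical status at each stated time point, reporting the common odds ratio with its 95% confidence interval.
- Remove the Wilcoxon test of change in the ordinal scale, which this model replaces.
- Keep the Wilcoxon test of status, if wanted, as a supportive analysis.
- Analyse NEWS with a baseline-adjusted ordinal or rank-based model if a baseline NEWS is collected. Otherwise leave it as it is.

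The cost is wording only: no new data, visits or patients. The small downside is reliance on proportional odds, which the plan already accepts for clinical status and against which the supportive Wilcoxon offers a check.
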